**Table** **2: Summary of literature about intervention studies for child** **undernutrition.**

| **Author** | **Year of publication** | **Place** | **Methodology** | **Findings** | **Gaps/ limitations** |
| --- | --- | --- | --- | --- | --- |
| Gulden GS, et al[21] | 2000 | China | Quasi-experimental study.  495 children were enrolled at 4–12 months.  Monthly growth monitoring and counseling by community-based/Village nutrition educator.  Pre-post 1-year program. | The education group infants were significantly heavier and longer at 12 months (weight for age -1.17 vs. -1.93, height for age -1.32 vs. -1.96) as compared to control group. | Weak supervision of community based village educators.  No baseline assessment was done in the study. |
| Pachón H, et al[38] | 2002 | Vietnam | Randomized effectiveness trial.  238 children age 5–25 months were enrolled.  2 weeks long daily nutrition education sessions per month for nine months.  Monitoring of growth was done monthly. | Intervention children consumed 20% (70 g) more food per day as compared to control children at 12 months.  More intervention children(40%) had met energy requirement. | Amount of food served to children was not taken into account and latest energy values of foods were not calculated. |
| Bhandari N, et al[20] | 2004 | Haryana, India | Randomized control trial  1025 newborns were enrolled  Nutrition counseling at monthly home visit for 12 months by ANM, AWW and HW.  Pre-post 18-month program. | Small but significant increase in length was seen intervention group (0.32cm, 0.03).More effect in male infants(0.51 cm, 95% CI 0.03, 0.98). no effect on weight.. Signiﬁcantly more energy intake was found in the nine month old infants in intervention group. | As the study was funded, so it may be difficult to replicate it in a resource constrained circumstances. |
| Penny ME, et al[19] | 2005 | Peru | Randomized Control Trial.  Birth cohort of 377 infants were enrolled and followed up from 0-18 months of age.  Intervention constituting of nutrition education was delivered through health services through by nutritional counseling. | Children in intervention group gained 295 g weight and they were 1 cm taller control group at 18 months of age. More caregivers in the intervention area reported that they received nutrition advice from the health workers than the control group (52% vs.. 24%). | This study may be difficult to replicate in areas where access to food is a limiting factor. |
| Kilaru A, et al[54] | 2005 | India | Effectiveness study  242 infants age 5-11 months were enrolled.  Nutrition education was delivered every month to caregivers by locally trained counsellors | Velocity of weight of female infants was more in the intervention group.  They had a morefrequency of feeding, more diverse diets. They had more chances to be fed complementary foods. | Assessment of diet was not done.  Field research staff was specially recruited for the study purpose only, hence the effect may not be sustainable in community. |
| Roy SK, et al[22] | 2007 | Bangladesh | Randomized control trial.  605 children age 6–9 months were enrolled in community nutrition centres.  Nutrition education given weekly for 3 months and then biweekly for 3 months  with the help of community based health workers.  6-month follow-up | Infants in the intervention group gained more weight than the control group after six month intervention (0.86 vs. 0.77kg, p = 0.053) and after one year observation period (1.81 vs. 1.39 kg, p < .001) | As the study was funded, so it may be difficult to replicate it in a resource constrained circumstances. |
| Zaman S, et al[51] | 2008 | Pakistan | Randomized control trial  375 children at the age of 6 to 24 months were enrolled.  5 1⁄2 days training for LHV using IMCI training, they visited the mother- and child pairs at home within two weeks, then at 45 days, and after 180 days of enrollment | More intervention mothers offered animal foods to their children (p=0.03 and 0.01). At the 3^rd^ visit, the mean SD score for WAZ more in intervention group (−1.17 vs. −1.7, p=0.012) | Only 58% of the trained LHV could perform adequately on observation; most mothers in the intervention group received only one counseling session. |
| Rao S, et al[55] | 2011 | India | Cross sectional study  Mothers of children 6 months – 2 years.  Semi structured questionnaires.  Study duration – 2 months. | Complementary feeding was started by 77.5% mothers had started at six months but complementary feeds was given by only 32% of mothers in adequate amounts. | Hospital based study so it can’t be used to represent the value in the general population.  Recall bias may be more.  The feed consistency was not taken into account. |
| Khan ZA, et al[52] | 2013 | Pakistan | Intervention study.  586 children between 6 months – 8 years of age.  Intervention strategy-nutrition education (individual counseling sessions targeting the mothers) | About 36% children in Tando Jam and 32% children in Quetta gained normal status of nutrition. Significant increase in the number of meals was observed. (Tando Jam-𝑃≤0.000/Quetta-𝑃≤0.025). | Short period of intervention.  Long term changes should be assessed in the population. |
| Kushwaha KP, et al[53] | 2014 | India | Quasi experimental study conducted over 5 year period.  Mother infant pairs were recruited.  Mother support groups provided counseling and support to the mothers. | Complementary feeding was started at the age of 6–8 months in 85% vs. 54% 2 years old children and in 5 year olds was 96% vs. 54%.  Complementary feeding along with continued breast feeding up to 2 years of age at both 2 years (36% vs. 4.5%); and 5 years (42% vs. 4.5%) as compared to pre-intervention period. | Project was funded so it may be difficult to replicate in resource constrained setting. |

Most of the studies included formative research but there was no pilot testing of the intervention in these studies [19–22]. They involved community health workers and nutritionist as facilitators of intervention but primary caregivers were not directly trained. The health workers working in public health sector has been used in few studies [19,20]. It is our understanding that if community workers are involved in delivering the intervention, then the benefit will reach more people and intervention will likely to be sustainable in a community. None of the studies conducted in India have explored the concept of tracking for undernutrition among children. There is lack of intervention studies on improving feeding practices and undernutrition in children among migrants in India. Since migrant population is on the rise in the country [56], and they are most vulnerable population especially their children in terms of higher morbidity and mortality, hence it is essential to focus on this group to prevent the most common underlying cause of morbidity and mortality among these children i.e., malnutrition. The present study is planned to assess the effectiveness of a nutritional education intervention by involving the primary care givers/mothers and health workers catering to vulnerable and migrant population in Chandigarh. The health workers will use the indivisualized approach and provide culturally appropriate nutritional counselling at home and support the mothers in infant feeding practices. The growth monitoring will done every month through monthly work plan for ANMs and *anganwadi* workers, so that they can focus on mother-infant dyads with low infant growths.

**Research question**

Whether culturally appropriate nutrition educational intervention delivered through health services can improve growth and complementary feeding of infants of age 6 months to 1 year old in Chandigarh?

**Null Hypothesis**

Culturally appropriate nutrition educational intervention delivered through health services has no effect on improving growth and complementary feeding of infants of age 6 months to 1 year old in Chandigarh.

**Aim**

To assess the effectiveness of culturally appropriate nutrition educational intervention delivered through health services to improve growth and complementary feeding by infants of age 6 months to 1 year old in Chandigarh.

**Objectives**

- To ascertain the effectiveness of a culturally appropriate nutritional education intervention delivered through health services to improve the growth and complementary feeding of infants of age 6 to 12 months in Chandigarh.
- To develop a child undernutrition tracking module for health workers to monitor child growth.

**METHODOLOGY**

**Study area:**

This study will be conducted in Chandigarh, Union territory. The population of Chandigarh is 1,054,686 with 1,19,434 children below the age of 6 years as per 2011 census.[57] About 97% of population resides in urban area. Out of which about 30% of the population resides in resettlement colonies. The female literacy rate is 81%.[57]

**Study design**

The study design will be quasi-experimental. The study and control area will be selected purposively. Study area will be Burail, an urbanized village in the catchment area of Civil Hospital, sector 45, Chandigarh. It is also one of the field practice area of department of Community Medicine, School of Public Health, PGIMER, Chandigarh. The population of Burail is 47,869 with 862 children below 1 year of age, as per annual health survey report, 2015-16. Most of the residents are migrants from neighboring states like UP, Bihar, Uttarakhand, Haryana and Himachal Pradesh, and belong to low or middle socio-economic groups. About 97% of children aged between 12 to 23 months in Burail are fully immunized, as per annual health survey report, 2015-16. Burail has 7 auxiliary nurse midwives (ANMs) and 19 anganwadi workers and centers. The control area will be Maloya, another urbanized village in Chandigarh. The background characteristics of control area are similar to study area in terms of vulnerability, migration of population, geographical location, socioeconomic status and baseline child health status. It has a population of 28,176 with 483children below 1 year of age as per annual health survey report 2015-16 of Civil Dispensary, Maloya. Maloya has 3 ANMs, 1 ASHA, 26 *anganwadi* workers and centers. About 90% of children aged 12-23 months are fully immunized in this area as per annual health survey 2015-16.

**Study population**

The study population will be mother-infant dyad with infant in age group 4-6 months at enrollment;auxiliary nurse midwives (ANM) and *anganwadi* workers (AWW) in the study and control area.

**Inclusion criteria**

1. Mother-infant dyad with age of infant between 4 to 6months of age.
2. Parents who are residing in the study area for the past 6 months and have no plans to migrate during the intervention period.
3. Mothers, ANMs and *anganwadi* workers who will give consent to be the part of the study.

**Exclusion criteria**

1. Severely ill infant or infant having clinical complications requiring hospitalization.
2. Infants with cerebral palsy or other congenital anomalies/malformations.

**Sample size:**

The sample size for the study is calculated by using the formula = (u+v)²*(σ₁²+σ₀²)/(µ₁-µ_0_)²

where

u=two sided percentage point of normal distribution corresponding to 100% - power=1.28

v=percentage point of normal distribution corresponding to (two sided) significance level=1.96, assuming 80% power with 95% C.I. [58].

(µ₁-µ₂)= difference between the means

d₁, d₀ = standard deviations

Difference between the mean weights is assumed to be 250 g [20].

Sample size thus calculated to be= [(1.28+1.96)²*((0.65)^2^+ (0.65)²]/ (0.25)² = 182. This is the minimum sample size of infants to be included in the study per arm.

Considering attrition rate of 10%, sample size per arm = 202.

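### The sample-size line does not reproduce: its printed inputs give 142 per arm, not 182, and its 1.28 is the power term for 90% power, not the stated 80%

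*Protocol*

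**What the plan says.** The whole calculation stands in the Sample size section of the protocol's Methodology. It uses the standard formula for comparing two means: the squared sum of a power term u and a significance term v, times the sum of the two variances, divided by the squared difference.

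- Power term: "u=two sided percentage point of normal distribution corresponding to 100% - power=1.28".
- Significance term and stated power: "v=percentage point of normal distribution corresponding to (two sided) significance level=1.96, assuming 80% power with 95% C.I".
- Difference: 250 g, with a citation to the Haryana randomised trial (reference 20).
- SD: 0.65 in each arm. It appears only in the worked line, without unit or source; kg is implied by the 0.25.
- Result: "182. This is the minimum sample size of infants to be included in the study per arm".
- Attrition: "Considering attrition rate of 10%, sample size per arm = 202".

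No other section of the protocol restates or corrects the calculation.

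**The concern.** The stated power, the normal quantile used and the resulting sample size should all follow from one another. Here no two of them agree. The worked line does not evaluate to its own answer, and the quantile does not belong to the power named beside it.

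The number is used: the Sampling Technique section continues enrolment until the required size is reached in both areas, and the Sample size section treats 182 as a floor. As the text stands, a reader cannot tell what power the study was designed for, nor which SD and difference the planned number rests on.

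**Working it through.** **Inputs**, all from the Sample size section: u = 1.28, v = 1.96, SD = 0.65 in both arms, difference = 0.25 kg, attrition 10%.

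**Step 1. The worked line as printed.**

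n = (u + v)² × (SD² + SD²) / difference²

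- (1.28 + 1.96)² = 3.24² = 10.4976
- 0.65² + 0.65² = 0.845
- 0.25² = 0.0625
- n = 10.4976 × 0.845 / 0.0625 = 141.93, so 142 per arm (143 with unrounded quantiles)

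The protocol prints 182, which is 40 per arm (28%) more than 142.

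**Step 2. The attrition step.** 182 / 0.9 = 202.2, printed as 202. This step is consistent with 182, so 182 is the figure that was carried forward and not a stray character in the text. From 142 the same step gives 142 / 0.9 = 157.8, so 158.

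**Step 3. The power term.** For 80% power, 100% minus power is 20%. The two-sided 20% point of the normal distribution is 1.28, which is what the protocol's definition of u delivers. But the power term needs the one-sided point. The one-sided 20% point is 0.84; 1.28 is the one-sided 10% point, which corresponds to 90% power. With u = 0.84:

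- n = (0.84 + 1.96)² × 0.845 / 0.0625 = 7.84 × 0.845 / 0.0625 = 106.0
- so 106 per arm, or 107 with unrounded quantiles
- with attrition: 106 / 0.9 = 117.8, so 118; 107 / 0.9 = 118.9, so 119

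**Step 4. What 182 per arm gives on the printed inputs**, assuming independent infants:

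- SE = 0.65 × √(2/182) = 0.0681
- 0.25 / 0.0681 − 1.96 = 1.71, a power of about 95.6%

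| Basis | Per arm | With 10% attrition |
|---|---|---|
| Stated 80% power (u = 0.84) | 106–107 | 118–119 |
| Printed u = 1.28 (90% power) | 142–143 | 158–159 |
| Stated result (about 95.6% power) | 182 | 202 |

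**Step 5. Can any ordinary variant give 182?** With the same SD and difference:

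- one-sided 5% test: 84 at 80% power, 116 at 90%
- small-sample correction (adding 1.96²/4 to 141.93): 143
- 95% power (u = 1.64 or 1.65): about 175 to 176
- v = 2.58: about 158 with u = 0.84, about 201 with u = 1.28

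None gives 182.

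**Step 6. Which input would have to differ?** Holding the difference at 0.25 kg:

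- with u = 1.28: SD = √(182 × 0.0625 / (2 × 10.4976)) = 0.74
- with u = 0.84: SD = √(182 × 0.0625 / (2 × 7.84)) = 0.85

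Holding the SD at 0.65 with u = 1.28, the difference would have to be √(10.4976 × 0.845 / 182) = 0.221 kg. None of these values appears in the protocol.

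**The case against.** Three points can fairly be made for the protocol.

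- **The 1.28 follows from the protocol's own definition.** A two-sided point for 20% is indeed 1.28. This stands, and it locates the second error precisely: the definition of u is wrong, not the table look-up. The resulting calculation is still not one for 80% power.
- **On the printed inputs the slip is conservative.** 182 exceeds both recomputed values, so this error does not underpower the study or bias its estimate. That also stands. It limits the consequence but does not make the statement correct.
- **The SD may be the misprint, not the result.** An SD of about 0.74 with u = 1.28 would give 182. This cannot be excluded.

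The third point also blocks some stronger readings. A reader might infer that 182 is inflated by 28% to 72% (182/142 and 182/106) and that enrolment may be reduced. That presumes the inputs are right and the result wrong, which the protocol does not show. The inputs have loose ends of their own. The 250 g is attributed to a trial for which the protocol's Table 2 records no weight effect. The SD has no source. The calculation is for mean weight, whereas the primary outcome is mean change in weight for age and effectiveness is assessed by a difference in differences; whether 0.65 is an SD of weight or of change is not said.

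A reader might also infer that an inflated target lengthens enrolment, because the control area lists only 483 children under one year. The protocol gives no accrual calculation from which to establish that.

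Finally, 182 might be read as 142 with a design effect of 1.28 for clustering. That ratio is simply 182/141.93. The protocol states no intracluster correlation, cluster size or clustering allowance. With one purposively chosen area per arm, area and intervention are fully confounded, so a design effect could not secure the nominal power.

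**Conclusion.** The point holds as two errors in one calculation. The arithmetic is wrong whatever the intended design, because the printed expression is 142 and not 182. The definition of u is wrong for a power term, so the stated 80% does not match the 1.28 used.

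The 95.6% figure is conditional on 0.25 kg and 0.65 being right for the comparison actually analysed, and on infants being independent. It describes the printed inputs and is not an estimate of the study's true power. The documents do not settle which of the result, SD, difference and power is the mistaken figure. The finding is therefore that the stated sample size and power are unsupported as written, not that the study is too large or too small.

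**What to change.** Define u as the one-sided normal point for 100% minus power. Then do one of the following:

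1. State the intended power, SD and difference, each with its source, and say whether the SD is of weight or of weight change. Recompute both 182 and 202 from them and print a worked line that evaluates to its stated result.
2. Keep 182 and 202, remove the claim of 80% power and the equation that does not equal 182, and state that 182 per arm gives about 95.6% power for a 0.25 kg difference with SD 0.65, assuming independent infants.

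Do not lower the enrolment target until the inputs are confirmed, and do not justify 182 by a design effect.

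Keeping 182 and 202 costs protocol wording only. Under the first route, any change in numbers depends on the inputs the investigators confirm.

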**Sampling Technique**

A list of all mother-infant dyads, where age of infants will be between 4 to 6 months, will be obtained from the *anganwadi* centers of the study and control area. Mother-infant dyads will be selected by simple random sampling in study and control groups from the complete list. Final inclusion will be done for those mother-infant dyads who will meet the study criteria. In the first month of enrolment, all mother-infants dyads between four to six months old infant will be enrolled. Enrollment will be continued thereafter till the required sample size is achieved in both study and control groups.

**Study duration**

1 year (July 2016- June 2017)

**The study will be conducted in four phases:**

1. **Pre-intervention phase**

***Formative research***

Focus group discussions (FGDs)will be conducted separately with each group of mothers, ANMs, AWWs and community representatives to explore the culturally appropriate foods for infants, gap between knowledge and action of mothers, frequency of infant feeding, feeding practices etc, using FGD guide, till data saturation (Annexure 1). Result of the FGDs will help in the modifying the nutritional education intervention as per the need of mothers and health workers, and development of child undernutrition tracking module for monitoring and supervision of child growth by health workers. Pilot testing of the intervention will be conducted in an area similar to the study area but not in study area.

1. **Baseline Assessment**

Baseline assessment of maternal knowledge of infant feeding, infant feeding practices by 24 hour dietary recall (frequency of feeding, number of meals and snacks per day) and hand hygiene practices will be done by using a pretested semi-structured questionnaire (Annexure 2). Feeding on the day before the interview will be used to represent the infant feeding practices. The status of under-nutrition will be assessed by baseline anthropometry of the infants by using Digital Salter Model 235, CMS weighing equipment and stadiometer (SECA height board UNICEF) for measuring weight for age, weight for length and length for age [59,60]. The knowledge of ANM and *anganwadi* workers on infant feeding and status of growth monitoring will be checked by a pre tested semi-structured questionnaire (Annexure 3). It will be assessed in both study and intervention arm.

**3. Intervention Phase**

***a. Intervention for mothers/ caregivers:***

The intervention will be delivered in community settings at mother-infant dyad level. The intervention duration will be six months. Mothers/caregivers will be provided nutritional education as per the modules.

**Module for mothers**: The content is consistent with age specific feeding recommendations made by World Health Organization, 2001 [61]. Culturally appropriate food recipes will be standardized and delivered with the help of dietician (co-guide).

**Nutritional Education & counseling** (for mothers) – Two sessions of nutrition education and counseling will be conducted for the mothers/caregivers.

- 1^st^sessionwill be conducted when the infants will be 6-8 months old.
- 2^nd^ session will be conducted when the infants will be 9-11 months old.

Both the sessions will be centered on feeding of infants, maintaining hygiene while cooking and eating and sanitation. Each session will last 30-45 minutes and will be conducted for 20-30 participants. Talks, group discussion and demonstration will be used to impart knowledge and skills of mothers related to infant and child feeding.

The control group will continue to receive standard care through routine health education offered by ANMs and *anganwadi* workers.

***b. Intervention for health workers***

**Module for Health workers –** The module will have three parts and will be delivered as:

- Part 1--- orientation and introduction
- Part 2 --- communication skills
- Part 3 --- home visit tasks and procedures

The ANMs will be trained as nutrition counselors. They will receive training at baseline and the session will be repeated after 2 months. After the training, the ANMs will conduct a fortnightly home visits to counsel and support mothers for infant feeding practices. Supervisory visits will be conducted by the resident every two months to assess their work.

A sensitization meeting with families, ANMs and AWWs responsible for child health will be conducted before the training of mothers and another meeting will be conducted after two months. ANMs/ AWWs will visit the mothers/care givers in their homes fortnightly/monthly. They will prepare an individualized plan of each mother-infant dyad for infant growth based upon the family’s acceptability of food and affordability. They will observe how mother is feeding the baby, hand hygiene practices. They will accordingly counsel them and improve the feeding practices. They will also resolve any problem mothers are facing while feeding the baby. They will also organize the monthly group meetings of the mothers. In these meetings mothers will get a chance to learn from the peers whose child are showing weight gain and will be motivated through positive deviance model[38].

1. ***Supervision of health workers***
   1. A module will be developed for tracking of undernourished child. The infants will be weighed every month in the *anganwadi* centers. The anthropometric data of the infants will be entered in an excel sheet in computer and z score will be calculated. A monthly work plan showing the nutritional status will be prepared for each child in the study area. This work plan will be given to all the ANMs and *anganwadi* workers in the area, so that they can focus on mother-infant dyads with low infant growth.
   2. About 10% of the counseling sessions by the health workers with the mother-infant dyads in the field will be directly observed and supervised by the junior resident in the study area, and accordingly feedback to the health workers and mothers will be given.

